The last challenge is obtaining the data from individual organisations. Most do not have single unified systems, so patient admissions, antibiotic usage (bulk DDDs or individual level prescriptions) and *C. difficile* data are all held on separate databases and have to be extracted, merged and pseudo-anonymised by overworked information technology departments. This is proving to be a significant challenge despite £14,000 per organisation being provided to obtain these data four times over the course of the trial (for Data Monitoring Committee [DMC] meetings and final analysis).

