For analyses comparing periods before and after introduction of the intervention, we hypothesise that the intervention could produce either a step change in each outcome, or ongoing changes over time (i.e. an interaction between intervention vs control and calendar time), or both. Analysis will therefore use an interrupted time series (ITS) analysis which not only estimates whether the intervention has a direct immediate impact, but also whether it has any impact on year-on-year trends after implementation (and compared with year-on-year trends pre-implementation) (Fig. 2). For example, even if there is no immediate impact of the intervention on mortality, it will be particularly important to monitor, say, whether any calendar year trends suggest mortality increases post-implementation. It will also be important to monitor whether antibiotic use declined faster post- vs pre-implementation.

Other reasons for using the ITS approach within organisation, and then pooling organisation-level estimates, are that many other things are likely to be changing differently in different organisations, and within organisations, over calendar time. For example, financial incentives could be introduced to reduce antibiotic use in hospital and increase the numbers of antibiotic prescriptions that receive review (under the Commissioning for Quality and Innovation [CQUIN]) payments framework). These external factors will affect within-organisation comparisons less than between-organisation comparisons. Further rates may not be constant before or after the intervention. Finally the calendar-time blocked randomisation makes the assumptions underlying the standard vertical comparisons (between organisations already randomised to intervention vs not at each step) more questionable. The date of introduction of the intervention will be the planned date of implementation for the feasibility and internal pilot organisations and the date that each organisation was randomised to implement the intervention in the main trial. Sensitivity analyses for the main trial will also consider the fact that implementation may occur gradually over approximately 3 months [56], by incorporating a trend for the 3 months post-implementation date instead of a single step change at the implementation date. The DMC will be asked to advise on the most appropriate analysis model as part of their Charter.

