### Oversight

An independent DMC will review outcome data from the phase III main trial approximately 6 months after it starts and then approximately every 9 months. The DMC is advisory: after each meeting they will make a recommendation that the trial continue, or be stopped or modified to the Programme Steering Committee which will meet every year throughout the programme. The DMC will consider both clinical and statistical evidence. Statistical evidence would be based on the Haybittle-Peto rule (*p* < 0.001 for impact of the intervention): this has the advantage that the number of DMC meetings does not have to be pre-specified in advance, and the DMC can meet more frequently as determined by the data. The DMC would consider both co-primary outcome measures in their deliberations regarding trial stopping. Further details of DMC functioning and the procedures for interim analysis and monitoring will be specified in a DMC Charter. The Programme Steering Committee is the executive body. This independent oversight committee is termed a Programme Steering Committee rather than a Trial Steering Committee because the trial is part of a larger programme, and the Programme Steering Committee provides consistent independent oversight across the entire programme of related work.

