### Main trial status

The first organisation was randomised in the main trial on 13 November 2017 (under protocol version 4.0) to implement on 12 February 2018. The last organisation is planned to be randomised on 1 April 2019 to implement on 24 June 2019.

The current protocol is version 5.0 (5 November 2018). All protocols have been approved by the South Central Oxford C Research Ethics Committee (REC) (17/SC/0034) and the Confidentiality Advisory Group (CAG) (17/CAG/0015). Protocol 1.0 (16 December 2016) was submitted for REC and CAG approval for the three phases of the study. Version 2.0 (24 March 2017; phase I feasibility study) incorporated clarifications requested by REC and CAG including those on opt-out and the electronic health records analysis population, and increased preparation time from randomisation to implementation from 3 to 4 months based on experience preparing for the feasibility study. Version 3.0 (25 September 2017; phase II pilot study) included further clarifications on the analysis population based on advice from the Nuffield Trust and extension of process evaluation to include interviews. Version 4.0 (6 November 2017; phase III main trial) returned preparation time from 4 to 3 months based on experience in the internal pilot and removed an acceptability rating which had not been collected. Version 5.0 (5 November 2018) increased the number of organisations included in process evaluation and clarified how individuals would be recruited for these qualitative studies, adding eight criteria defining implementation fidelity and several other clarifications regarding objectives, outcome measures, withdrawal, population and analysis to align with the statistical analysis plan version 1.0.

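### A primary analysis model is named, but the committee that sees interim outcomes is also asked, without limit, to advise on the analysis model

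*Protocol article*

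**What the plan says.** The Statistical analysis section of the protocol article specifies a primary analysis. Mortality is modelled by logistic regression and DDDs by negative binomial regression. Each organisation is fitted separately with a trend before implementation, a trend after it and a step at implementation. The organisation estimates are then pooled by meta-analysis, and the primary comparison tests step and trend change jointly on 2 degrees of freedom. A gradual-implementation variant, "by incorporating a trend for the 3 months post-implementation date instead of a single step change at the implementation date", is labelled a sensitivity analysis and is later listed among the secondary analyses. Seasonal terms may be added if investigation shows a need.

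Directly after that variant the section adds: "The DMC will be asked to advise on the most appropriate analysis model as part of their Charter".

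The Oversight section states: "An independent DMC will review outcome data from the phase III main trial approximately 6 months after it starts and then approximately every 9 months". On what the committee weighs, it says: "The DMC would consider both co-primary outcome measures in their deliberations regarding trial stopping". It also says "The DMC is advisory", names the Programme Steering Committee as the executive body, and leaves details of DMC working and interim monitoring to the Charter. Under Outcomes and their assessment, organisations are funded "to obtain these data four times over the course of the trial", covering DMC meetings and the final analysis.

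**The concern.** Two statements in one section are not reconciled. One fixes the primary model. The other refers the choice of model to a committee that sees accumulating results on both co-primary outcomes. The second carries no restriction to interim work, no date by which advice must be given, and no requirement that it be given without sight of results.

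A step, a 3-month ramp and a seasonally adjusted step give different estimates from the same data. If the choice among them is informed by post-implementation results, the selected analysis no longer has the error rate of a model fixed in advance. That applies to a false claim of an effect and to a false claim of non-inferiority. The trial is unblinded, compares before with after, and has a 5% relative margin on mortality, so readers need assurance that the model was settled independently of the results.

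**Working it through.** The point is procedural and the protocol gives no figure to reproduce. The check has two parts.

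**1. The texts side by side**

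- Model named: yes (Statistical analysis).
- DMC asked about the model: yes, in the same section, with no limit on outcome, stage or timing.
- DMC sees outcomes: yes, at about 6 months and then about every 9 (Oversight). Four extracts less one for the final analysis leaves about 4 − 1 = 3 interim looks.
- Any text requiring the advice to precede outcome review, or to be blind to it: none in the article.

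The route is open on the wording.

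**2. How much could model choice matter?**

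Inputs from the Sample size section: 36 organisations, two implementing per month for 18 months, then 12 months' follow-up; 5000 to 15,000 admissions a year plus one organisation of 25,000; 30-day mortality uniform on 7% to 10%.

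Assumptions: 24 months of pre-implementation data, and a month-to-month SD of the mortality probability of 0 or 0.01. The Sample size section prints 0.1 for that SD. It was not used for the table because, in short runs of 300, the upper limit for the fixed model then fell below 1.05 only about 6% of the time. That is a separate matter.

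Models, restricted to those the section names or allows:

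- A: step + trend change (the stated primary model)
- C: 3-month ramp + trend change
- E: A plus seasonal terms

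Each organisation's monthly log-odds were fitted by weighted segmented regression with estimated dispersion. Estimates b_j with covariance V_j were pooled with fixed effects:

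b = (Σ V_j⁻¹)⁻¹ Σ V_j⁻¹ b_j, with V = (Σ V_j⁻¹)⁻¹

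- Joint test: bᵀV⁻¹b against chi-squared on 2 df at 5%.
- Non-inferiority: estimated immediate effect + 1.96 × SE < ln(1.05) = 0.0488.
- Most favourable choice: smallest p-value, or smallest upper limit, among A, C and E.

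Results from 2500 runs per setting:

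| Quantity | SD | A fixed | Best of A, C, E | Difference (points) |
|---|---|---|---|---|
| Two-sided error, no effect | 0 | 4.44% | 6.32% | 6.32 − 4.44 = 1.88 |
| Two-sided error, no effect | 0.01 | 6.60% | 8.52% | 8.52 − 6.60 = 1.92 |
| False non-inferiority, true OR 1.05 | 0 | 2.52% | 3.24% | 3.24 − 2.52 = 0.72 |
| False non-inferiority, true OR 1.05 | 0.01 | 3.00% | 4.20% | 4.20 − 3.00 = 1.20 |

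The comparison should be read within rows. The rise in the A column from 4.44% to 6.60% comes from the SD setting, not from model choice. Simulation error for a single entry is about 0.4 points (√(0.05 × 0.95 / 2500) = 0.0044).

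A simpler check agrees: 20,000 single null series, 24 months before and 18 after, gave about 5% for one fixed model and 6.9% for the better of step-plus-slope and ramp-plus-slope.

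**The case against.** The strongest reply is that the primary model is not open. It is stated down to the test, and the ramp is only a sensitivity or secondary analysis. This stands: a reader of the DMC sentence alone might infer that the primary model was left blank, and the rest of the section shows otherwise.

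Second, the sentence refers to the Charter, which Oversight describes in terms of interim work, and the Haybittle-Peto rule (p < 0.001) needs a model to produce a p-value. Advice on the monitoring model is therefore a natural reading, and the Charter or SAP may say so. This is plausible, but the sentence sits among the final-analysis methods and carries no interim qualifier. What is at issue is an unrestricted statement in the protocol, not a detail left to another document.

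Third, the DMC is independent and advisory, the Steering Committee decides, and the DMC has no stated reason to prefer a favourable result. A model that favours one co-primary outcome need not favour the other, and success requires both. This stands, and it makes the simulated figures upper bounds.

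A reader might also infer from the dates that the advice is sought after the first outcome review. Six months from first randomisation (13 November 2017) is May 2018, and from first implementation (12 February 2018) is August 2018. Protocol version 5.0 is dated 5 November 2018. The inference fails: the article uses the same future tense for the review and the Charter, does not say which version introduced the sentence, and gives no meeting dates.

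**Conclusion.** The concern holds in a limited form. The article names a primary model and, in the same section, asks a committee with access to results to advise on the analysis model without restricting that advice. A results-informed change to the primary model is possible on the text; nothing shows that one occurred.

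The size is modest. Under the assumptions above, always taking the most favourable of the three models adds about 1.9 points to the two-sided error and 0.7 to 1.2 points to false non-inferiority. These figures come from mortality only; DDDs were not simulated. The non-inferiority check uses only the upper limit of the immediate effect.

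A reader might infer larger inflation by adding a step with a common trend and a step with no trend, which raises the two-sided error to 11.6% to 14.5% and false non-inferiority to 5.2% to 6.8%. The protocol names neither model as a candidate, so those figures should not be attributed to it. Nor do the documents support saying that the safety conclusion is already undermined.

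**What to change.** Replace the DMC sentence in the Statistical analysis section with:

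> The primary analysis model is that stated here and in the SAP. The DMC may advise on the model used for its own interim monitoring; any change to the primary model is proposed by people without access to post-implementation outcome data, approved by the Programme Steering Committee and dated.

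Align the SAP and the Charter with this wording. If the DMC has already advised on the primary model after seeing outcome data, report the date and present the pooled step-and-trend analysis with its joint 2-df test alongside whatever was adopted.

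The cost is a short text change in three documents. The loss is that the primary model no longer benefits from DMC advice informed by accumulating data.

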### Outcomes and their assessment

The main primary and secondary outcomes will be assessed using anonymised routine electronic health records data that are already captured at participating organisations. These data will be extracted from NHS databases and anonymised by local organisation informatics/information technology departments (funding is provided to support this) before sending to the research team, following a pre-defined data specification document detailing data items and coding. All patients can request that their NHS records not be released for secondary use (for example, in Hospital Episode Statistics (HES)). Patients who have opted out of sending their hospital records to NHS Digital will not have information submitted for intervention evaluation.

The phase III main trial has two co-primary outcomes:30-day mortality post-admission (non-inferiority)DDDs of antibiotics per acute/general medical admission (superiority).

Admission (rather than bed-day) is the denominator for this co-primary outcome (similar to the DH Antimicrobial Prescribing Quality Measures), because bed-day can be strongly influenced by non-medical reasons for not discharging inpatients [46, 47]. The reason for including two co-primary outcomes is to include both a patient health outcome, where we expect to see no evidence of benefit from using fewer antibiotics, but importantly no evidence of harm; and also an endpoint reflecting the overarching goal of the intervention, namely to reduce antibiotic use. However, the full trial will not evaluate a shorter course of antibiotics per se, but an intervention designed to reduce antibiotic duration enacted through healthcare professionals’ behaviour. There is therefore no guarantee that it will have the desired effect on total antibiotic usage: if the intervention does not reduce antibiotic consumption, de facto it will have failed. For this reason, antibiotic consumption is a co-primary superiority endpoint. The fact that the primary endpoint (30-day mortality) is for non-inferiority is another reason for including antibiotic duration as a co-primary endpoint; the intervention will be considered successful only if it significantly reduces antibiotic usage with no evidence of increased mortality.

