Each outcome will first be modelled separately in each organisation, estimating trends before and after intervention implementation, plus an implementation-associated immediate effect (‘step change’) (Fig. 2). The unit of analysis will be admission. Patient will be used as a clustering variable for robust variance adjustment (but not otherwise adjusted for). Based on data available to date, we do not expect strong seasonal effects in the outcomes above, but this will be investigated and included if necessary. Meta-analytic techniques will then be used to combine these organisation-specific estimates to produce an overall intervention effect, assessing heterogeneity using *I*^2^ statistics. This approach is similar to a multilevel model, but it has more flexibility in modelling individual organisations. The primary comparison will be a 2 degree of freedom test, jointly testing that the ‘step change’ is zero and that there is no change in calendar trends post- vs pre-implementation. This joint test will be fitted on model parameters and explicitly account for correlation between the two estimands. Secondary analyses will consider calendar trends post-implementation, and change in calendar trends post- vs pre-implementation, and a trend for implementation over 3 months rather than a ‘step change’.

The major concern about unadjusted analyses is the potential for variation in case mix, particularly over a calendar year, to affect estimates of intervention effect. Additional sensitivity analyses will adjust for case mix to assess whether changes in case mix could confound any changes in antibiotic use observed over time. The following admission-level covariates have been chosen based on their significant effects on 30-day mortality in previous analyses of emergency admissions from routinely collected data [57] and will be adjusted for in each organisation regardless of statistical significance (with non-linear relationships between covariates and outcomes assessed and incorporated using natural cubic splines): sex; age (years) at admission; immunosuppression; Charlson Co-Morbidity Index (defined using secondary diagnosis codes); interaction between age and Charlson [57]; patient classification; admission method, source, specialty, day of the week, time of day and day of year and interaction between admission day of the week and time of day [57]; number of admissions in previous year (excluding as day case), and ever had a complex admission.

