### Sample size

For the phase III main trial, based on simulation studies, the proposed stepped-wedge cluster-randomised design including data from a minimum of 36 organisations has > 85% power to exclude a 5% relative increase in 30-day mortality and to detect a 15% relative reduction in antibiotic use associated with the intervention. The 5% relative non-inferiority margin means that to declare non-inferiority, the entire 95% confidence interval (CI) for the relative change in mortality post- vs pre-intervention has to lie within [0.95,1.05]. For an overall mortality of 9%, this is analogous to being confident that the post-intervention mortality lies within [8.5%, 9.5%], that is, a non-inferiority margin of +/− 0.5% on the absolute scale or 5% on the relative risk or relative odds scale (which are similar given the low event rates).

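### The primary 2-df joint test has no direction and is not linked to the 5% mortality margin, and the plan does not say which contrast of the step-plus-slope model the margin applies to

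*Protocol article*

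**What the plan says.** Under Statistical analysis, each outcome is modelled separately in each organisation, "estimating trends before and after intervention implementation, plus an implementation-associated immediate effect". Meta-analysis is then used to "combine these organisation-specific estimates to produce an overall intervention effect"; which parameter or time point that effect refers to is not stated. The decision step follows: "The primary comparison will be a 2 degree of freedom test". Its null hypothesis has two parts, a step of zero and equal slopes on either side of implementation. The same section expects that the intervention may act as a step, as a change that develops over time, or as both, and singles out as important "whether any calendar year trends suggest mortality increases post-implementation".

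The hypotheses are directional. The Objective has mortality non-inferior and DDDs per admission superior. The Sample size section gives the non-inferiority rule: the whole 95% "confidence interval (CI) for the relative change in mortality post- vs pre-intervention has to lie within" the range from 0.95 to 1.05. It also states power above 85% with at least 36 organisations, from a simulation with no time trends in either outcome. Outcomes and their assessment adds a success criterion in other words: the intervention succeeds only if it "significantly reduces antibiotic usage with no evidence of increased mortality".

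**The concern.** Three statements bear on the mortality decision: a joint zero-null test, a CI containment rule, and a requirement of no evidence of increased mortality. They are not connected and can disagree. The joint test reacts to any departure from no change, whether a fall, a rise, or a fall followed by a rise. The CI rule needs a single ratio, while a step-plus-slope model gives a different ratio at each month until a time or an average is fixed. The third statement, read literally, could be met by an imprecise estimate.

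Both co-primary conclusions are at stake. If the contrast is chosen once the data are in, that choice can settle whether the intervention is called safe.

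**Working it through.** **Inputs from the Sample size section.** 36 organisations; 5,000 to 15,000 admissions a year (uniform) plus one organisation of 25,000; 30-day mortality uniform on 7 to 10%; two organisations implementing per month for 18 months, then 12 months of follow-up; no true mortality effect; 95% CI within [0.95, 1.05].

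**Assumptions where the article is open.**
- Length of the simulated pre-implementation period: 12 or 24 months. Follow-up asks for data from two years before phase III, or as near to that as possible.
- The monthly mortality SD of 0.1 has no stated scale. It is read here as negligible (0 to 0.1 percentage point), with a 10% relative SD as an alternative.
- Fixed-effect inverse-variance pooling unless stated.

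**The plan's own figure.** Power above 85% is an inequality with open inputs, so it cannot be reproduced exactly. The step contrast with negligible SD is compatible with it. With 0.1 taken literally on the probability scale, power is 0 with over-dispersion-adjusted standard errors, and 0.21 for the step with model-based ones.

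**1. The joint test has no sign.** With 24 months of pre-data, SE(step) = 0.0109, SE(slope change per year) = 0.0098 and correlation r = −0.26, all on the log-odds scale. With z1 = step/SE and z2 = slope change/SE, the non-centrality is (z1² + z2² − 2·r·z1·z2)/(1 − r²).
- Step OR 0.95 (log −0.0513): z1 = −4.71, z2 = 0, so 22.1/0.932 = 23.7; rejection probability 0.995. The mirror image, OR 1.053, gives the same 0.995.
- Step −5% with slope change +6% per year: non-centrality about 46; rejection probability 1.000. The OR runs 0.95 at month 0, 1.01 at month 12 and 1.07 at month 24.
- Step 0 with slope change +3% per year (OR 1.06 at month 24): rejection probability 0.80, so it is missed with probability 0.20. With 12 months of pre-data it is missed with probability 0.52.

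**2. The margin has several possible targets.** The log effect t years after implementation is step + t × slope change, with variance SE(step)² + t²·SE(slope)² + 2·t·r·SE(step)·SE(slope). At t = 1 this is 0.000119 + 0.000096 − 0.000056 = 0.000159, so SE = 0.0126.

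With no true effect, power of the containment rule is Φ((0.0488 − 1.96·SE)/SE) − Φ((−0.0513 + 1.96·SE)/SE), since ln 1.05 = 0.0488 and ln 0.95 = −0.0513. At 24 months (SE 0.0198) this is Φ(0.50) − Φ(−0.63) = 0.43. The other entries are simulated (200 runs per setting); the formula agrees closely.

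| Contrast | SE, 24 months pre-data | Power | SE, 12 months pre-data | Power |
|---|---|---|---|---|
| Step | 0.0109 | 0.985–0.995 | 0.0120 | 0.975–0.98 |
| Effect at 6 months | 0.0107 | 0.99 | 0.0141 | 0.885–0.895 |
| Effect at 12 months | 0.0126 | 0.96 | 0.0186 | 0.54–0.60 |
| Effect at 24 months | 0.0198 | 0.43 | 0.0303 | 0 |

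The last entry is 0 because the CI is 2 × 0.0594 = 0.119 wide and the interval from ln 0.95 to ln 1.05 is only 0.100 wide.

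**3. How the possible rules behave when harm builds.** A second set of simulations (24 months of pre-data) gives SEs for the step, the 0–12 month average and the 12-month effect of 0.0115, 0.0108 and 0.0128 with binomial noise only, and 0.0157, 0.0146 and 0.0174 with a 10% monthly SD and random-effects pooling. The normal approximation gives the probability that the upper limit is below 1.05 (binomial / 10% SD):
- Step 0, slope +5% per year (OR 1.05 at 12 months). The step passes in 99% / 87%; under two-sided containment, 98% / 78%. The 0–12 month average (log 0.0244) passes in 62% / 39%. The 12-month effect passes in 2.5%, because the truth sits on the margin.
- Step −5%, slope +10% per year (0.95 × 1.10 = 1.045 at 12 months). The average (log −0.0036, ratio 0.996) passes in 99.8% / 95%. The 12-month effect passes in 5.6% / 4.6%.

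**4. Power of the 12-month effect with a 10% monthly SD.** With SE 0.0174, the upper-limit rule gives Φ(0.0147/0.0174) = 0.80, and containment gives 0.80 − Φ(−0.0172/0.0174) = 0.80 − 0.16 = 0.64.

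**The case against.** A reader might infer that the plan rests non-inferiority on the joint test. It does not: the Sample size section supplies a CI rule, and says that the aim is to place the CI inside the margin and not to find a significant difference. What is missing is the link between the two and the contrast.

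A reader might also infer that the model cannot yield a relative change, or that a fall in DDDs cannot be shown. Both go too far. A ratio at any chosen time follows from step and slope. A significant joint test with both DDD coefficients negative would read as a fall. Only opposite signs are unresolved, and the plan gives no rule for them.

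Nor do the documents say that slowly building harm would be declared non-inferior. That needs the margin to be applied to the step alone, which is stated nowhere. With step 0 and +5% per year the joint test itself rejects in more than 99% of trials, and the plan undertakes to examine trends. The two rules would then disagree, with nothing to say which governs.

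The strongest defence is that the exact contrast is normally SAP detail, and the article says that protocol version 5.0 was aligned with SAP version 1.0, which is not shown; the analysis-model figure is not shown either. That defence covers what is left unsaid. It does not cover what is said: an undirected zero-null test is named as the primary comparison for a non-inferiority and a superiority claim.

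**Conclusion.** The point holds in this form. The stated primary comparison does not by itself decide either co-primary hypothesis, and the CI rule for mortality has no named estimand once step and slope can differ. The simulation hides this because, without trends, the step is the whole effect. The choice matters: power for one and the same rule runs from about 0.99 (step) to 0.43 (24-month effect) with two years of pre-data, and from about 0.98 to 0 with one year. The figures rest on the assumed pre-period, a negligible monthly SD and fixed-effect pooling. The absence of sign and the undefined contrast rest on the text alone.

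**What to change.** In Statistical analysis and Sample size, state that each co-primary is decided by the 95% CI of one pre-named, directional contrast, computed from step and slope change with their covariance and pooled over organisations.

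- **Mortality:** choose a contrast that captures building harm, such as the effect at 12 months (step plus one year of slope change), judged against 1.05. An average over 0–12 months alone is not enough, since it can pass an early fall followed by a rise. If the two-sided containment rule is replaced by an upper-limit rule, say so openly.
- **DDDs:** superiority if the upper 95% limit of the named ratio is below 1.
- **Supporting results:** keep and report the 2-df test, the step and the slope change.
- **Success criterion** in Outcomes and their assessment: replace the no-evidence-of-increase wording with non-inferiority by the Sample size rule.
- **Power:** restate it for the named contrasts, with the pre-period length and the scale of the monthly SD.

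The cost is more than wording. Containment power for the 12-month mortality effect is about 0.96 with 24 months of pre-data and negligible monthly variation, but 0.54 to 0.60 with 12 months. With 24 months and a 10% monthly SD it is about 0.64 (0.80 under an upper-limit rule), below the stated 85%. No DDD power for a named contrast with trends has been worked out here.
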